(4) Frail elderly patients	(4.1) Assessment of community-based integrated care services for frail patients at BSA	(4.1) Prospective controlled cohort study using PSM methods (2018) (Additional file 4: Table S4)	(4.1) Individuals enrolled in BSA integrated care programs for frail elderly that includes: i) Early Discharge support (*n* = 144); ii) Long-term home-based support services (*n* = 566) and iii) Geriatric residences care (*n* = 920)	(4.1) Individuals living in Badalona receiving usual care: i) After hospital discharge (n = 144), ii) At home (n = 566); and, iii) Living at geriatric residences (*n* = 920)	(4.1a) Cost-effectiveness of the service; and, expanded HDA using MCDA (n = 250). Factors modulating success of the implementation strategy.
					(4.1b) KPI for service assessment

**Abbreviations**: *HDA* Health Delivery Assessment, *MCDA* Multi-Criteria Decision Analysis, *HCB* Hospital Clinic de Barcelona, *PSM* Propensity Score Matching, *KPI* Key Performance Indicators for service long-term assessment after the deployment phase, *BSA* Badalona Serveis Asssistencials

**Table 2 Tab2:** Three main assessment dimensions: effects of the intervention, determinants of success of implementation and maturity of integration

Study Protocol	Outcomes of the intervention [26, 27]		Deployment strategies [28, 29]	Maturity level [4]

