(1) Population-based	Mortality, general practitioner visits, community-nurse visits, cumulative days per year admitted in hospital, emergency department visits, all hospital admissions, potentially avoidable hospitalizations, multiple drug prescription, needs for social support, costs per patient per year (Additional file 1: Table S1)		A. What are the possible factors and agents responsible for good implementation of a health intervention? B. What are the possible factors for enhancing or expanding a given health intervention? C. What describes the context in which implementation occurs? D. What describes the main factors influencing implementation in a given context? To be assessed using a mixed methods approach: combining qualitative and quantitative methods	Assessment of the twelve dimensions of the Maturity Model for Integrated Care, both at health system and health services levels, promoted by the European Innovation Partnership for Active and Healthy Ageing, following the instructions reported in reference (4). These twelve dimensions are: 1. Readiness to Change 2. Structure & Governance 3. Information & eHealth Services 4.Standardization& Simplification 5. Finance & Funding 6. Removal of Inhibitors 7. Population Approach 8. Citizen Empowerment 9. Evaluation Methods 10. Breadth of Ambition 11. Innovation Management 12. Capacity Building
(2) Home hospitalization	Health and well-being	Mortality rate 30/90 days after discharge, place of death, avoidable hospital admissions, total bed days, 12 months before admission (hospital and community resources); 30-day after discharge (hospital and community resources), transitional care strategies (palliative care, primary care or hospital care)		
	Patient experience	Person centeredness, continuity of care (Additional file 2: Table S2)		
	Costs	Operational costs		
(3) Prehabilitation	Health and well-being	Cumulative hospital days of stay, intensive care unit length of stay, number of complications per patient, costs from the perspective of the hospital including inpatient services, diagnostic procedures, pharmaceutical consumption and blood products consumption, aerobic capacity, physical activity, psychological status, health status (Additional file 3: Table S3)		
	Costs	Operational costs		

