#### Assessment protocol 2: home hospitalization (HH)

The intervention group to be analysed will include all the patients admitted to HH and early discharge service from HCB during a one-year period (October 2017–October 2018) (*n* = 1146), approximately 70% of the patients were admitted to HH directly from the emergency room. A subset of the patients admitted to HH directly from the emergency room throughout the study period will be assessed separately (*n* = 200).

The characteristics of the intervention have recently been described by Hernandez et al. [13] in terms of implementation strategy, outcomes and costs during the deployment of the service in a real-life setting during the years 2006–2015. During the period 2017–2018, the programme was expanded to 48 beds per day to cover the entire AISBE health district.

The principal objective of this protocol is to assess hospital avoidance and early hospital discharge at health district level. Moreover, the approach aims to generate recommendations for shared-care agreements between specialized and community-based care after discharge to ensure safe transitional care strategies.

The assessment protocol will consist of a prospective controlled cohort study wherein patients admitted to HH directly from the emergency room (intervention) (*n* = 800) will be compared with conventional hospitalisation (control) (*n* = 800). The control group will include patients admitted to conventional hospitalization directly from the emergency room of the same hospital (HCB). PSM will be used for comparability purposes using age, sex, GMA, socioeconomic status, number of hospitalisations during the previous year and polypharmacy as matching variables. As described above, a sub-group of 200 consecutive patients recruited on a voluntary basis, admitted through the emergency department during the study period, from each arm (HH and conventional hospitalization) will be also thoroughly characterized using a set of standardized questionnaires [26, 27, 30], as depicted in Tables 2 and Additional file 2: Table S2. It is of note that these two well defined sub-groups of 200 patients each (*n* = 400) will also constitute a single fixed cohort for later analysis on the interactions between specialized and community-based care using network and cluster analyses alongside qualitative methodologies.

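### Home hospitalization: patients enter both arms at emergency-room admission, but mortality and one resource-use item are counted from discharge, which leaves out index-episode deaths and can start the clock at different times in the two arms

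*Protocol article*

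**What the plan says.** **Entry.** Under Assessment protocol 2, "patients admitted to HH directly from the emergency room (intervention) (*n* = 800) will be compared with conventional hospitalisation (control) (*n* = 800". On the controls: "The control group will include patients admitted to conventional hospitalization directly from the emergency room of the same hospital (HCB". Both arms therefore start when the patient leaves the emergency room for HH or for a ward.

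**Adjustment.** "PSM will be used for comparability purposes using age, sex, GMA, socioeconomic status, number of hospitalisations during the previous year and polypharmacy" are the matching variables. All describe the patient before treatment.

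**Outcomes.** The HH row of Table 2, under health and well-being, begins "Mortality rate 30/90 days after discharge, place of death, avoidable hospital admissions, total bed days". It continues with two resource windows, "12 months before admission (hospital and community resources" and "30-day after discharge (hospital and community resources". Place of death, avoidable admissions, total bed days and operational costs are listed with no time window. No mortality from admission and no in-episode mortality is listed for this protocol. Additional file 2: Table S2 is cited but not shown.

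**Aim.** "The principal objective of this protocol is to assess hospital avoidance and early hospital discharge at health district level". A further aim concerns shared-care agreements and safe transition after discharge.

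**The concern.** The arms separate at the emergency room, yet the mortality clock starts at discharge. This has two consequences.

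First, a rate counted after discharge can include only patients who survived to discharge. Deaths during the period when the two arms actually receive different care fall outside it.

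Second, discharge may come at different points after admission in the two arms. If risk is highest early and then falls, the arm discharged sooner carries more of the high-risk period into its post-discharge window. A difference can then appear when none exists, or a real one can be masked.

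Both problems arise after treatment starts, so matching on baseline variables does not remove them. The resource-use item has the same anchor: one window ends at admission and the other begins at discharge, so between them they skip the index episode. At stake is whether the HH and ward arms can be compared on mortality at all, since this is the only mortality rate listed for the protocol.

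**Working it through.** **Cohort size.** The article gives no mortality rate, effect size or power for Protocol 2, so the only figure to reproduce is the arm size. It reports 1146 HH patients, about 70% of them directly from the emergency room: 0.70 × 1146 = 802, consistent with 800 per arm.

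**Uncounted deaths.** Deaths left out = 800 × index mortality. The document gives no index mortality, so a range is assumed:
- 0.5%: 800 × 0.005 = 4
- 2%: 800 × 0.02 = 16
- 5%: 800 × 0.05 = 40

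**Effect of unequal start times with no true difference.** Assume the same daily hazard from admission in both arms, h1 for days 0 to 10 and h2 afterwards. The cumulative hazard is H(t) = h1·min(t, 10) + h2·max(0, t − 10). With an index episode of L days:
- index deaths = 800 × [1 − exp(−H(L))]
- 30-day risk from discharge = 1 − exp(−[H(L + 30) − H(L)])
- 30-day risk from admission = 1 − exp(−H(30))

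Worked case, h1 = 0.004, h2 = 0.001, L = 5 v 8 days:
- L = 5: H(5) = 0.020 and H(35) = 0.065. Risk from discharge = 1 − exp(−0.045) = 4.4%; index deaths 16.
- L = 8: H(8) = 0.032 and H(38) = 0.068. Risk from discharge = 1 − exp(−0.036) = 3.5%; index deaths 25.
- From admission, both arms: H(30) = 0.060, risk 5.8%.

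| h1, h2 per day | From discharge, 5 v 8 days | Spurious difference | From admission, both arms | Uncounted deaths of 800 |
|---|---|---|---|---|
| 0.002, 0.0005 | 2.2% v 1.8% | 0.4 points | 3.0% | 8 v 13 |
| 0.004, 0.001 | 4.4% v 3.5% | 0.9 points | 5.8% | 16 v 25 |
| 0.006, 0.001 | 5.3% v 3.9% | 1.4 points | 7.7% | 24 v 37 |

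Swapping which arm has the longer episode reverses the sign. With equal episodes (7 v 7 days) the spurious difference is zero, but 11 to 33 deaths per arm are still uncounted. All hazards and episode lengths are assumptions.

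**Meaning of discharge in the HH arm.** If it meant leaving the emergency room rather than the end of the home episode, home-episode deaths would count while ward deaths would not. With 1 v 7 days and hazards 0.004 then 0.001, the risk from discharge would be 5.5% v 3.8%, again with no true difference.

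**The case against.** Post-discharge windows are a natural choice for the transitional-care aim, and mortality is one item in a list, not a named primary outcome for Protocol 2. Table 2 is a summary, and the unseen Table S2 may define discharge or add an in-episode measure. Every rate above is assumed; with equal episode lengths the timing artefact vanishes, and its sign depends on which arm stays longer.

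Most of this stands, and it limits the point. It justifies keeping the post-discharge figures as secondary measures. It does not remove the mismatch, because the printed definition itself fixes the clock at discharge. A supplement could add a measure, but the definition as stated would still need changing for an HH-versus-ward comparison.

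A reader might infer more in four places, and the document does not support it:
- *All resource use is affected.* Only the 30-day item carries a discharge anchor. Total bed days, avoidable admissions and operational costs have no stated window and may include the index episode.
- *Listing place of death shows that home deaths are lost.* That item has no window either. It may record deaths during the episode, and it is also meaningful for later deaths.
- *The early-discharge service in Protocol 4 has the same fault.* Table 2 gives frail-elderly mortality no discharge anchor. The Table 1 wording "Individuals living in Badalona receiving usual care: i) After hospital discharge (n = 144" labels the control setting, alongside home and residence, and does not state a time zero.
- *A risk ratio can be attached to the bias.* That needs in-episode mortality in each arm, which the document does not give.

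**Conclusion.** The point holds for two Protocol 2 items: mortality at 30 and 90 days, and hospital and community resource use at 30 days. Entry is at admission, the clock starts at a post-treatment event whose timing the service is meant to change, and that event is not defined for the HH arm in the shown text. The listed mortality rate therefore leaves out index-episode deaths and may compare the arms over different stretches of illness.

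Direction and size are unknown. Under assumed index mortality of 0.5% to 5%, 4 to 40 deaths per arm of 800 go uncounted. Under the assumed hazards and a 3-day difference in episode length, the artefact in 30-day mortality is about 0.4 to 1.4 percentage points, against zero when counted from admission. These figures show that the problem is not negligible by construction; they do not predict this study's result.

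**What to change.** For Protocol 2, count all-cause mortality to day 30 and day 90, and hospital and community resource use to day 30, from the date of admission from the emergency room. Use the same fixed windows in both arms, analyse by initial allocation (HH or ward), and include the index episode. Define discharge separately for each arm. Keep the post-discharge figures as secondary measures for the transitional-care aim, described as conditional on surviving to discharge.

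The cost is low. The change is to outcome definitions, not to recruitment or matching. The existing outcomes already need dates of admission, discharge and death, and the article already draws on the regional registry, which covers hospitalization and emergency events, and on health records. The main extra work is to bring index-episode use into the 30-day resource item on the same basis in both arms.

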### Assessment protocols

#### Assessment protocol 1: population-based analysis

This protocol will take into consideration the entire population of healthcare users in Catalonia. The health system in Catalonia (7.5 M inhabitants) has three organisational levels, with the seven health regions at the top level (Fig. 2). Each region includes several geographical areas called health districts, second level, covering both specialised and primary care needs of the population. The third level corresponds to clusters of primary care centres within each healthcare district. The region has a total of 369 primary care units covering approximately 20 k citizens, on average, each of them.

**Fig. 2 Fig2:**
[figure not shown]
The figure displays the seven health regions of Catalonia. The urban area of Barcelona (1.8 million citizens) has four health districts. The South-Eastern healthcare sector of the Barcelona city, which encompasses 520 k inhabitants, is Barcelona-Esquerra (AISBE). Taken from the Catalan Health Service (CatSalut) website. https://catsalut.gencat.cat/ca/coneix-catsalut/transparencia/territori/informacio-cartografica/mapes/ This is a public access image.

Integration of health and social services in the entire Catalonia is being promoted under the umbrella of the five-year regional health plans. Key goals in terms of deployment of the integrated model were established during the 2011–2015 Plan [11] and consolidation of the program is expected during the 2016–2020 period [12].

The Integrated Health District in Barcelona-Esquerra (AISBE) (*n* = 520 k inhabitants) [19] is the intervention district and includes HCB as reference centre, two general hospitals and 19 primary care centres run by different healthcare providers. Since mid-2000s, AISBE has deployed, and continuously developed, IC services for chronic patients across healthcare tiers [9, 19]. Deployment of IC services in AISBE is based on the hypothesis that an appropriate transfer of selected care complexities from hospital-based to community-based care, within an IC scenario, can increase healthcare value generation both at provider and at health system levels. The main characteristics and achievements of technologically-supported IC services evaluated and adopted in AISBE have been reported elsewhere [8, 9, 14, 16, 19, 43].

The main objective of this assessment protocol is the analysis of health-value generation of IC in Catalonia (Table 1). An ancillary aim is to enhance health risk assessment for clinical purposes and service selection, taking into account the population-based risk assessment tool, (i.e. GMA), as reported in [39]. For the principal objective, health-related outcomes in AISBE will be compared using a case-control design with three other healthcare districts of the city of Barcelona (approximately 400 k inhabitants each), and the entire region (7.5 M inhabitants), considered as control areas. A PSM method will used for comparability purposes using age, sex, health-risk grading based on GMA [39, 42], and socioeconomic status as matching variables*.* Comparisons between intervention and controls will be done on a yearly basis for the period 2011–2017. Key specific aspects of the assessment protocol are summarized in Additional file 1: Table S1.

Health risk assessment and service selection will address enrichment of the predictive role of standard clinical information using population-based health risk assessment (GMA grading) and patient self-tracked information obtained through the regional personal health folder in Catalonia (La Meva Salut). Evaluation of resulting clinical predictive modelling (Table 1) will be based on fixed cohort study designs with 1 year follow-up, as already reported in [40].

#### Assessment protocol 2: home hospitalization (HH)

The intervention group to be analysed will include all the patients admitted to HH and early discharge service from HCB during a one-year period (October 2017–October 2018) (*n* = 1146), approximately 70% of the patients were admitted to HH directly from the emergency room. A subset of the patients admitted to HH directly from the emergency room throughout the study period will be assessed separately (*n* = 200).

The characteristics of the intervention have recently been described by Hernandez et al. [13] in terms of implementation strategy, outcomes and costs during the deployment of the service in a real-life setting during the years 2006–2015. During the period 2017–2018, the programme was expanded to 48 beds per day to cover the entire AISBE health district.

The principal objective of this protocol is to assess hospital avoidance and early hospital discharge at health district level. Moreover, the approach aims to generate recommendations for shared-care agreements between specialized and community-based care after discharge to ensure safe transitional care strategies.

The assessment protocol will consist of a prospective controlled cohort study wherein patients admitted to HH directly from the emergency room (intervention) (*n* = 800) will be compared with conventional hospitalisation (control) (*n* = 800). The control group will include patients admitted to conventional hospitalization directly from the emergency room of the same hospital (HCB). PSM will be used for comparability purposes using age, sex, GMA, socioeconomic status, number of hospitalisations during the previous year and polypharmacy as matching variables. As described above, a sub-group of 200 consecutive patients recruited on a voluntary basis, admitted through the emergency department during the study period, from each arm (HH and conventional hospitalization) will be also thoroughly characterized using a set of standardized questionnaires [26, 27, 30], as depicted in Tables 2 and Additional file 2: Table S2. It is of note that these two well defined sub-groups of 200 patients each (*n* = 400) will also constitute a single fixed cohort for later analysis on the interactions between specialized and community-based care using network and cluster analyses alongside qualitative methodologies.

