**Fig. 1 Fig1:**
[figure not shown]
The figure depicts the main elements of the structured evaluation framework that articulates the four assessment protocols described in the current report. The proposed comprehensive assessment of integrated care services includes their impact at population level. A core component of the assessment protocols includes the identification of Key Performance Indicators (KPI) useful for long-term follow-up of health services after adoption encompassing three dimensions: health outcomes, processes and structure

The Catalan Health Care System dispenses services for 7.5 inhabitants, providing universal coverage through a tax-based system. Administratively, it is composed by a single public payer and multiple service providers publicly or privately owned. Since 2006, the implementation of IC services in one of the four healthcare sectors in the city of Barcelona (520 k inhabitants) was instituted by the Hospital Clinic of Barcelona (HCB), a tertiary university hospital [19], adopting the Chronic Care Model as the conceptual reference [20, 21]. Moreover, the subsequent Health Plans for Catalonia after 2011, have addressed the deployment challenges by giving priority to new modalities of healthcare delivery for chronic patient care including empowerment of patients and carers. To date, clear examples of clinical effectiveness have been produced for the three IC services presented in this report: Home hospitalization [13, 22, 23], prehabilitation [14] and community-based services for frail patients [9]. It is expected that lessons learned from the implementation of the four protocols reported in the current manuscript will foster regional scalability and sustainability of IC services in Catalonia. Moreover, it is also expected that the recommendations generated by these deployments in real-life settings will significantly contribute to facilitate transferability and comparability of IC services at international level. The context in which these four assessment protocols will take place is described in [11] and [19].

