## Methods

The four protocols (Table 1) follow observational and experimental non-randomized study designs. In all cases, comparability between the intervention group and the control group will be achieved using a propensity score matching (PSM) [24, 25] method, as described in detail below. The common methodology for assessing health-value generation of the interventions in each protocol will follow a Quadruple Aim approach [17, 18] considering pre-defined variables for: i) Health and well-being; ii) Experience with care; iii) Operational costs; and, iv) Health professionals’ engagement, as summarized in the second column of Table 2. It is of note that the outcomes of the three first dimensions (Triple Aim approach) [26, 27, 30] will be assessed both separately and jointly. The later will consist of a multi-criteria decision analysis (MCDA) recently developed [31, 32] and currently applied in 17 selected IC programs from 8 European countries [33]. The MCDA approach broadens the scope of the evaluation taking into account patient health reported outcomes and stakeholders’ views on those same outcomes allowing standardized comparisons between seemingly dissimilar IC programmes. Moreover, engagement of health professionals, the fourth pillar of the Quadruple Aim approach, will be assessed using the questionnaires currently applied in [34], aiming at assessing main drivers of large-scale deployment of IC services in 5 European regions.

**Table 1 Tab1:** Main characteristics of the four assessment protocols

Protocol	Aims	Study design & Measurements	Intervention group	Comparator group	Expected outputs
(1) Population-based study	(1.1) Impact of integrated care on cost-effectiveness	(1.1) Case control study matching registry data using PSM methods (2011–2017) (Additional file 1: Table S1)	(1.1 and 1.2) Residents living in the healthcare district of Barcelona-Esquerra (*n* = 516 K inhabitants)	(1.1 and 1.2) Residents living in the other 3 healthcare districts of Barcelona (~ 400 k inhabitants each), as well as the entire region of Catalonia (*n* = 7.5 M inhabitants)	(1.1a) Health value generation of integrated care
	(1.2) Enhanced health risk assessment and service selection	(1.2) Fixed cohort study			(1.1b) Enhanced Key Performance Indicators (KPI) for long-term assessment of integrated care
					(1.2) Proposal for health risk assessment for service selection

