(2) Home hospitalization	(2.1) Assessment of hospital avoidance and early hospital discharge at district level	(2.1) Prospective controlled cohort study using PSM methods (2017–2018) (Additional file 2: Table S2)	(2.1) All patients admitted to the home hospitalization directly from the emergency room (*n* = 800 patients). Study of a deeply characterized subset (triple aim approach) of 200 patients. This subset will be used to generate (2.2).	(2.1) Patients admitted to conventional hospitalization directly from the emergency department of the same hospital (n = 800 patients). Study of a deeply characterized subset (triple aim approach) of 200 patients. This subset will be used to generate (2.2).	(2.1a) Health value generation of the service; expanded HDA using MCDA (n = 200). Factors modulating success of the implementation strategy.
		(2.2) Observational mixed-methods study combining network and cluster analyses with qualitative methodologies			
	(2.2) Recommendations for shared-care agreements between specialized and community-based care				
					(2.1b) KPI for service assessment
					(2.2) Strategies for enhanced interactions between specialized-community-based care.
(3) Prehabilitation	(3.1) Sustainability (cost-effectiveness of prehabilitation at HCB	(3.1) Prospective controlled cohort study using PSM methods (2016–2018) (Additional file 3: Table S3)	(3.1) All candidates for major surgery at HCB receiving prehabilitation (*n* = 500)	(3.1) Candidates for major surgery at HCB receiving usual care in the same hospital (*n* = 250)	(3.1a) Health value generation of prehabilitation at HCB
	(3.2) Recommendations for transition toward a regional peri-operative care program	(3.2) Randomized controlled trial to assess peri-operative care	(3.2) Candidates for major surgery at HCB receiving peri-operative care (*n* = 60)		(3.1b) KPI for service assessment
	(3.3) Enhanced pre-operative risk assessment	(3.3) Fixed cohort study	(3.3) All surgical patients in the last 5 years at HCB	(3.2) Candidates for major surgery at HCB receiving usual care (n = 60)	
					(3.2) Cost-effectiveness of peri-operative care and strategies for regional deployment.
					(3.3) Risk assessment tool for personalized prehabilitation

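### Protocol 2 neither restricts nor matches on residence, so if the share of patients living outside AISBE differs between the arms, district care may enter the home hospitalization comparison

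*Protocol article*

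**What the plan says.** **The service and objective.** Assessment protocol 2 states that during 2017–2018 "the programme was expanded to 48 beds per day to cover the entire AISBE health district". Its principal objective is "to assess hospital avoidance and early hospital discharge at health district level".

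**The controls.** The same section says: "The control group will include patients admitted to conventional hospitalization directly from the emergency room of the same hospital (HCB". Table 1, row (2.1), gives the same definition: "Patients admitted to conventional hospitalization directly from the emergency department of the same hospital". Neither place mentions where the patient lives.

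**The matching.** The propensity score uses "age, sex, GMA, socioeconomic status, number of hospitalisations during the previous year and polypharmacy as matching variables". None of these is residence, health district or primary care area.

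**The hospital.** The Background describes "the Hospital Clinic of Barcelona (HCB), a tertiary university hospital". The section on Assessment protocol 1 adds that HCB is the reference centre of AISBE, a district that also has two general hospitals and 19 primary care centres.

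**District care as an exposure.** The section on Assessment protocol 1 says: "Since mid-2000s, AISBE has deployed, and continuously developed, IC services for chronic patients across healthcare tiers". Table 1 gives that protocol's intervention group as "Residents living in the healthcare district of Barcelona-Esquerra", compared with the other three Barcelona districts and all of Catalonia.

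**The concern.** One protocol treats AISBE residence as something that may change admissions, emergency visits and community contacts. Another protocol in the same article measures related outcomes and does not control for it. For Protocol 2, Table 2 lists hospital and community resource use in the 30 days after discharge, as well as transitional care. These outcomes depend partly on the community services to which the patient returns.

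The matching variables do not deal with this. Morbidity grading, earlier admissions and polypharmacy may absorb some of the pre-admission difference between districts. They do not balance the care available after discharge.

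Aim 2.2 is also exposed. The two subsets of 200 patients are pooled into one cohort to study how specialized and community care interact. Any patient living elsewhere would bring in primary care centres outside AISBE's own 19, in an analysis meant to support shared-care recommendations.

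**Working it through.** **The plan's own figure.** Assessment protocol 2 gives 1146 home hospitalization admissions, about 70% of them directly from the emergency room: 0.70 × 1146 = 802.2. This agrees with the stated 800 in the intervention arm, which is matched 1:1 to 800 controls. The article gives no effect size, alpha or power for Protocol 2, so there is no sample size calculation to reproduce.

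**Is residence controlled anywhere in the text shown?**
- Home hospitalization arm: all emergency-room admissions to the service. Coverage of AISBE is stated; no address rule is.
- Control arm: conventional admissions from the HCB emergency room. No address rule is stated.
- Matching: six variables, none geographic.
- Protocol 4 uses the same six variables but also states that its usual-care patients come from the same area. Protocol 2 states only the same hospital.

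**Size, under assumptions.** Let s be the share of matched controls living outside AISBE, h the same share in the home hospitalization arm, and D the difference in outcome risk between non-AISBE and AISBE patients. Then

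bias = (s − h) × D.

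The documents give none of the three. The values below are assumptions.

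| h | s | D = 2 points | D = 5 points |
|---|---|---|---|
| 0 | 10% | 0.2 | 0.5 |
| 0 | 20% | 0.4 | 1.0 |
| 0 | 30% | 0.6 | 1.5 |
| 0 | 40% | 0.8 | 2.0 |
| 10% | 0 | −0.2 | −0.5 |
| 10% | 10% | 0 | 0 |
| 10% | 40% | 0.6 | 1.5 |

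(Bias in percentage points.)

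**Effect on a test with no true service effect.** Assume a 20% event rate, 800 per arm, h = 0, and a two-sided 5% normal approximation for two independent proportions. For s = 40% and D = 5 points:
- the rates are 0.20 and 0.22;
- the standard error is √(0.20 × 0.80/800 + 0.22 × 0.78/800) = 0.0204;
- the shift is 0.02/0.0204 = 0.98 standard errors;
- the rejection probability is 16.6%.

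Across s = 10% to 40%, it is 5.1% to 6.8% for D = 2 points and 5.7% to 16.6% for D = 5 points, against a nominal 5%.

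**Direction.** The article's hypothesis for AISBE is that suitable care moves from hospital to community. If that is true, non-AISBE controls would have more hospital use, which favours home hospitalization. They might also have less community use, which counts against it on that outcome. The direction is therefore not the same for all outcomes.

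**The case against.** The strongest reply is that the article is silent on residence for both arms, and silence is not a rule. A reader might infer that controls are any emergency admission wherever the patient lives, that the service is tied to AISBE addresses, and that the comparison therefore must mix the two effects. The text supports none of these steps. Covering a district is not the same as excluding everyone else. As written, both arms are defined symmetrically by hospital and route. Additional file 2: Table S2 is not shown and may contain eligibility rules.

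The choice of hospital also limits the problem. HCB is AISBE's own reference centre, and every AISBE-resident control has the same district care as the home hospitalization arm. Using one hospital also keeps the emergency department the same for both arms. Matching on earlier admissions and morbidity covers part of the pathway. The article also says integration is promoted throughout Catalonia, and whether AISBE differs is what Protocol 1 sets out to test.

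All of this stands, and it makes the point conditional. It does not remove it. The article does fix the control source and the list of matching variables, and neither keeps the non-AISBE share equal between arms. Protocol 4 shows that the article states the controls' area where it means to.

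**Conclusion.** The point holds in conditional form. Nothing in the text shown makes the two arms alike in residence, and the article itself regards residence as potentially relevant to post-discharge hospital and community use. A difference in the non-AISBE share is plausible, because a home service built around a district is compared with emergency admissions at a tertiary hospital. It is not established.

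Size and direction cannot be determined from the documents. Under the assumed ranges with h = 0, the bias is 0.2 to 2.0 percentage points. It is negligible at the low end, while at the high end it is enough to raise the false-positive rate from 5% to about 17%. It is zero if s = h, and it reverses sign if h exceeds s. It would be wrong to conclude that the design as described necessarily favours home hospitalization: that needs an address rule, a known district effect and a uniform direction across outcomes, and the article supplies none of these. This is a cheap improvement to a stated design choice, not a fatal flaw.

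**What to change.** In the section on Assessment protocol 2 and in Table 1, row (2.1), state one residence rule and apply it to both arms before the propensity score is fitted. There are two ways to do this:
- restrict both arms to AISBE residents, which fits the district-level objective; or
- keep all patients and match exactly on health district or primary care area.

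Apply the same rule to the two 200-patient subsets. Report the share living outside AISBE in each arm, before and after matching. Filtering the controls alone should be avoided: if the home hospitalization arm contains any patients from outside AISBE, that would create the imbalance it is meant to remove.

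The data should be at hand, since the regional registry covers all residents of Catalonia and Protocol 1 already classifies patients by district. The cost is a somewhat smaller pool for matching and, under the restriction, possibly slightly fewer than 800 home hospitalization patients.
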